#### IETP Data Collection Content

In our project start-up, we are developing a preliminary IETP characterization table based on guidelines and subject matter expertise (refer to the preliminary summary in Multimedia Appendix 1). In tandem, using clinical team expertise and literature on evidence-based implementation strategies that are relevant to the IETP clinical components reviewed in the IETP characterization table, the process of implementation to date will be represented as a CFIR-based implementation research logic model (IRLM) [31]. The IRLM will use data on inputs, activities, and outcomes to specify the relationships among determinants of implementation, implementation strategies, and the mechanistic links between strategies and outcomes relevant to the following: (1) inputs—program referral patterns, characteristics of IETP patients, staffing and skills required to deliver the program, facilities, resources needed to deliver the program, and other program inputs evident in the literature review; (2) activities—set of therapeutic activities that comprise the program, characterized as core or peripheral and as individual or group interventions, along with the programmatic meetings and staff training that are necessary to deliver the program; and (3) outcomes—immediate and long-term outcomes that define program success [32]. The IRLM, contextualized by CFIR constructs, will be triangulated and analyzed as part of aim 1 and iteratively revised to reflect the clinical relevance for each site. The team will also refer to the validated inventory of implementation strategies in the development process by Powell et al [33]. The IRLM template is provided in Multimedia Appendix 10 [31].

#### Elicitation of IETP Contents and Operationalization

We will interview respondents to identify the inputs, activities, and outcomes that define the IETP. We will refer to the IETP characterization table to elicit inputs on convergence and divergence between their experience and the guidelines. The preliminary IETP characterization table will be used as a plausibility check for these initial interviews to evaluate, for instance, whether the elicited program inputs, activities, and outcomes are concordant with the published literature and whether the suggested links between program activities and outcomes are plausible. The analysis will be conducted within the context of CFIR to ensure strategic alignment with the implementation recommendations. The elicitation of program inputs, activities, and outcomes will be expedited by comparing similar products developed in the ORION project. ORION project library elements that correspond to IETP inputs, activities, and outcomes will be shared with the interviewees as examples. This process will support the iterative development of the IETP Care Implementation Elements Inventory. Multimedia Appendix 11 provides an example from the ORION project.

#### Data Analysis

Qualitative data collection and analysis will occur concurrently. Insights from the data analysis will be used to iteratively guide data collection. The evaluation team will work together to develop an a priori code book based on the 2009 CFIR constructs, as each interview guide is also based on the 2009 CFIR constructs. Transcripts, artifacts, and observation notes will be uploaded to ATLAS.ti 22 Windows software to organize and code data. Analysis methods will be used to identify domains related to data for specific data types, such as key informant interviews and focus groups [34]. Participant comments will be organized to develop codes and merged to develop categories. Categories will be compared, and relationships will be identified. Data samples will be extracted and coded by 2 project team members and evaluated for interrater reliability and credibility. The data sets for each site will be compared to determine the commonalities and differences between sites. The evaluation team will conduct a matrix analysis to analyze across-site domains and taxonomies [35]. Descriptive and comparative matrices will identify the patterns of regularities and inconsistencies and identify the relevant and representative components by site to support strategy development. Once cases and comparative matrices are developed, follow-up interviews will be reviewed by the stakeholder panel to verify the findings and provide additional input and clarification.

### Aim 2

Aim 2 will use the existing data to identify IETP participants; types of care received; and long-term outcomes, including postdischarge needs and trajectories, of IETP. The models will be reviewed with clinical partners throughout, with the final analytic output delivered at the end of year 2.

#### Measures and Data Collection Procedures

Data from each IETP participant will be obtained from site leads beginning with Tampa (2015 to present; n=approximately 350). We will obtain identifiers that allow linkage to VA and DoD health system data and create a study crosswalk database behind the VA firewall that includes the encrypted identifier, a study ID, and contact information for interview and survey administration. We will obtain intake and discharge measures from each IETP site. We will assess IETP fidelity based on the IETP characterization table (Multimedia Appendix 1) using a checklist (Multimedia Appendix 2) and chart abstraction focusing on the admission note, admission IETP care plan, discharge TBI care plan, and discharge summary, which are highly accurate in describing the reasons for seeking treatment, baseline status, the type of treatment recommended, the type of treatment received, and outcomes on discharge (Multimedia Appendix 12).

We will also link these IETP data to VA and DoD health system data, as we have done previously [36], to obtain information on physical and mental health, medications, and military demographic data before and after IETP. As approximately 90% (225/250) of participants in the IETP are active duty at the time of treatment with the goal of returning to full duty and operational partner priority outcomes include return to duty or employment, the use of VHA data (eg, Patient Health Questionnaire-9 [PHQ-9] and PTSD checklist-5) is not a feasible approach to long-term outcomes. Therefore, we will conduct a survey using a VA-approved web-based survey software for participants of IETP (2015-2022; approximately 500) using a Modified Dillman Method, which we used in prior VA studies (Multimedia Appendix 13) [37-40]. We will begin a survey of earlier IETP graduates in the first year of the study and send surveys to new graduates 6-9 months post study completion. The final outcome measures included in the survey will be developed in collaboration with stakeholders. The current list of stakeholder-identified measures that are evaluated at intake and discharge include the PHQ-9, PTSD checklist-5, MPAI, and the Neurobehavioral Symptom Inventory.

We will also use VA and DoD health system data to describe health system outcomes such as use, new diagnoses, and adverse outcomes, which will, together with data baseline, discharge, fidelity, and discharge outcomes, be used to develop trajectories of recovery.

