#### Identify Treatment Received During IETP

Consistent with prior studies [50-52], we will create an abstraction tool in collaboration with IETP clinicians and aim 1 data. Using the crosswalk database, we will conduct chart abstraction for IETP focusing on the initial assessment, TBI care plan, processes and amount of care received, discharge assessment, and TBI care plan. After finalizing the procedures and appropriate training, team members will independently review 10 charts and then meet to identify inconsistencies, errors, or disagreements and resolve any by consensus. This will continue until there is 90% agreement on all items abstracted, to ensure abstraction fidelity. The areas of uncertainty will be discussed with IETP clinicians. These data will be merged with IETP data, VA and DoD analytic file data, and survey data for the outcome analyses.

We will identify what happens during the IETP stay using descriptive statistics for the overall cohort, stratified by phenotypes from the measures listed in the *Measures and Data Collection Procedures* section. We expect that different types of care will be provided to individuals with different prior comorbidities and clinical presentations. We will apply Pearson chi-square test to assess the association between recommendations for admission TBI care plan and TBI phenotype.

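### Treatment received is coded from charts that also show the discharge outcome, and the 90% agreement check would not reveal coding that leans toward that outcome

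*Protocol article*

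**What the plan says.** Under Aim 2, *Measures and Data Collection Procedures*, the protocol article bases fidelity on a checklist and on chart abstraction. The charts are the admission note, the admission care plan, the "discharge TBI care plan, and discharge summary, which are highly accurate in describing" several things, among them "the type of treatment recommended, the type of treatment received, and outcomes on discharge". The same section says of the scored measures: "We will obtain intake and discharge measures from each IETP site".

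Under *Identify Treatment Received During IETP*, the abstraction is described as one exercise that covers the initial assessment, the care plan, "processes and amount of care received, discharge assessment, and TBI care plan". On the tool: "we will create an abstraction tool in collaboration with IETP clinicians and aim 1 data". On quality control, abstractors go through a set of 10 charts separately and settle their differences by consensus, with this stopping rule: "This will continue until there is 90% agreement on all items abstracted, to ensure abstraction fidelity". On doubtful items: "The areas of uncertainty will be discussed with IETP clinicians". The coded data are then merged with the other sources for the outcome analyses.

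Under *Identify Components of IETP Associated With Sustainment and Improvement Trajectories*, the coded treatments become nodes in a Bayesian network. It is built by hill-climbing on the Bayesian information criterion (BIC) and used to find the treatments with the better probability of a good long-term outcome.

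**The concern.** Whether a component was delivered, and how much of it, is partly a judgement made from free text. If the person judging has the patient's discharge status in view, an ambiguous note may be read as delivered when the patient did well and as not delivered when the patient did poorly. Discussing doubtful items with clinicians of the program does not remove this, because they may also know the outcome.

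An exposure error that depends on the outcome can produce an association between component and outcome where none exists. A larger sample does not reduce it, and bootstrapping the edges reproduces it, since every resample carries the same miscoded entries. The article intends the findings as the basis for implementing effective components and deimplementing ineffective ones, and *Potential Limitations* states that there is no comparison group.

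**Working it through.** The article gives no figure on this point, so there is none to reproduce. The check has two parts.

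**1. The text.**
- The source set for treatment received includes the discharge summary, and the article says this set also describes discharge outcomes. Coding treatment from it exposes the coder to outcome text.
- The abstraction content lists the discharge assessment beside the amount of care received.
- The stated check is agreement between abstractors. Agreement measures consistency: two people who read the same outcome text and lean the same way agree fully.
- Scored discharge measures come from the sites, so the abstractors do not need to supply them.

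**2. The possible size.** The inputs from the article are n = 500 (*Power and Missing Data*) and BIC edge selection. The assumptions, which the article does not give, are: no true effect; half of patients improve; delivered care is coded as delivered with probability s1 in improved and s0 in unimproved patients; undelivered care is never coded as delivered; true receipt is r.

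Coded receipt is a = r × s1 in improved patients and b = r × s0 in unimproved patients. The false odds ratio is [a/(1−a)] / [b/(1−b)].

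- r = 0.50, 95%/85%: a = 0.475, b = 0.425. OR = (0.475/0.525)/(0.425/0.575) = 1.22. Improved: 0.475/0.900 = 53% if coded as received, 0.525/1.100 = 48% if not.
- r = 0.80, 95%/85%: a = 0.76, b = 0.68. OR = (0.76/0.24)/(0.68/0.32) = 1.49. Improved: 0.76/1.44 = 53% against 0.24/0.56 = 43%.
- r = 0.50, 95%/90%: a = 0.475, b = 0.45. OR = 1.11.

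For one binary treatment and one binary outcome, BIC adds the edge when G² exceeds ln(500) = 6.21. Here G² = 2n Σ p ln(p/e), where p are the cell probabilities and e their values under independence. The last column allows for sampling variation.

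| Receipt | Coding | False OR | Expected G² | Chance that a false edge enters |
|---|---|---|---|---|
| any | equal | 1.00 | 0 | about 1.3% |
| 50% | 95%/90% | 1.11 | 0.31 | about 3% |
| 50% | 95%/85% | 1.22 | 1.26 | about 9% |
| 80% | 95%/85% | 1.49 | 3.98 | about 31% |
| 90% | 95%/85% | 1.81 | 6.63 | about 53% |
| 95% | 95%/85% | 2.21 | 9.25 | about 71% |

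A second error pattern serves as a cross-check, with receipt of 30% to 70%. A share f of non-recipients with a good outcome is coded as received, and the same share of recipients with a poor outcome is coded as not received. Expected G² is 1.3 to 1.5 at f = 5% (2.5% of charts miscoded), 5.0 to 5.8 at f = 10% (5% of charts) and 20.1 to 22.5 at f = 20% (10% of charts). In this pattern a false edge is expected once somewhat more than 5% of charts are miscoded in the direction of the outcome.

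**The case against.** The strongest reply is that the article does not describe who codes what. A reader might infer that one abstractor codes treatment and outcome in a single pass. The text says only that members of the team review charts; order of coding, masking and division of work may be set in the chart abstraction appendix, which is not shown. That stands, and silence on masking is not itself an error. The point needs less: the article names the discharge summary as a source for treatment received, so the coder of treatment has outcome text at hand unless something prevents it.

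A reader might also infer that the program's clinicians decide doubtful codes. The article says that such items are discussed with them and that abstractor disagreements are settled by consensus. It does not say that clinicians decide, or that they are told the outcome.

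Third, the route to bias is narrow. Outcomes are standardized measures from the sites and a later participant survey, not abstractors' judgements. Health system data also record the type of care during the stay (Table 4), although the article does not say that they are used to check the abstraction. This stands for long-term outcomes, which the bias reaches only through their correlation with discharge status. It stands less for discharge outcomes, which enter the trajectories directly.

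Fourth, the coding rates are assumed, the analysis is declared exploratory, and BIC screens out weak links. This also stands: at 50% and 80% receipt the expected G² is below the threshold. Fewer survey responses would lower it further for survey outcomes. The screen weakens when nearly everyone receives a component, which is plausible for core parts of a bundled program.

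Finally, withholding the discharge summary could lose information on care delivered. That is right, and the fix must keep it as a treatment source.

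**Conclusion.** The concern holds as a risk of differential exposure misclassification. The documents do not show that any bias has occurred or will occur. What they establish is that treatment received and fidelity are coded from charts in which the discharge outcome can be seen, that unclear items are discussed with IETP clinicians, and that the only stated quality check would not reveal a shared lean toward the outcome.

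The edges from treatment to discharge outcome are the ones mainly affected. The size is unknown. Under the assumed 95%/85% coding with no true effect, the false odds ratio is about 1.2 to 1.5 for receipt of 50% to 80%, and most samples of 500 would not yield a false edge. Only at receipt of about 90% or more, or with more miscoding, does a false edge become more likely than not. The point is worth settling because the remedy is cheap, not because a large distortion has been shown.

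**What to change.** 1. Take discharge scores only from the site files, and leave outcome items off the treatment and fidelity abstraction form.
2. Code treatment and fidelity items first from the care plans and treatment records, and lock them before the discharge assessment and the outcome text of the discharge summary are read.
3. Then add any treatment documented only in the discharge summary as a flagged entry. Rerun the network without the flagged entries as a sensitivity analysis.
4. Settle unclear items by a written coding rule, or with a clinician who is shown only the treatment text.

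The cost is a change to the form and to the order of work, slightly slower abstraction, a few flagged items and one additional network run. If the chart abstraction appendix already sets such an order, one sentence in the article saying so would close the point.

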**Results:**

Data collection began in December 2021 and is currently ongoing. The results and deliverables will inform IETP characterization, evaluation, implementation, and knowledge translation.

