**Data to knowledge (preimplementation stage)**			
	Aim 1: characterize consumer demand	IETP^e^ value from referrals within VA and DoD is unknown	Use of qualitative data collection with patients treated across fully and partially implemented sites
	Aims 1-2: fully characterize the innovation (IETP)	IETP is a black box with poor characterization to duplicate and sustain across systems	Use of qualitative interview technique and quantitative analyses of administrative data sets to identify effective practice core elements and adaptation options
	Aim 2: determine early and late outcomes from IETP	Outcome monitoring has not been the focus of the existing programs	Leverage existing data (eg, IETP data) and collect prospective outcome data to identify measures of success and establish baseline performance at the fully implemented site

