#### Characterize IETP Participants

We will begin characterization with the Tampa site (n=approximately 350) and Richmond site (n=approximately 150), followed by other sites. We will use VA and DoD health system data to characterize preadmission military and sociodemographic characteristics, TBI-related diagnoses (eg, PTSD, pain, and sleep), and medication use (eg, opioids, antidepressants, and sedative hypnotics). We will add data from TBI history and symptom inventories administered at IETP admission to develop mild TBI phenotypes [36,41,42]. This allows the characterization of participants in the IETP and the identification of groups that are likely to have similar courses of care.

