## Results

Funding and start-up activities for the evaluation began in April 2021, and the evaluation officially began in October 2021. Data collection is underway at all 5 sites and is expected to continue through May of 2025. Key informant and staff focus groups have been completed at 4 of 5 sites; the fifth site was launched in April of 2023. DoD and patient interviews are underway at all 5 sites, with one site observation to be conducted. Data analyses are underway. The anticipated evaluation results will be disseminated by 2024 and thereafter.

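### Survey follow-up runs from about 6 months to nearly 8 years, and the outcome network as described does not account for time since discharge

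*Protocol article*

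**What the plan says.** The Protocol article, Aim 2, Measures and Data Collection Procedures, gives the survey population as "participants of IETP (2015-2022; approximately 500". Timing depends on when a person graduated: "We will begin a survey of earlier IETP graduates in the first year of the study", and the plan will "send surveys to new graduates 6-9 months post study completion". Under Results, "the evaluation officially began in October 2021"; the abstract adds that "Data collection began in December 2021 and is currently ongoing".

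Table 3 lists four instruments at baseline, discharge and one survey occasion. Table 4 lists diagnoses, health care use, and medications and procedures in a column for the period after the program, with no stated length.

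The section on components associated with sustainment and improvement trajectories describes a network with three levels: phenotypes, treatment and outcomes. The probabilities to be reported are those of long-term outcomes given program components and comorbidity phenotype. Neither the levels nor the conditioning set includes time since discharge or year of admission, and the article mentions neither as an analysis variable.

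**The concern.** Survey answers given a few months after the program and answers given six or seven years after it share one table column and one network level. Time since discharge is almost fixed by discharge year. Anything else that changed with calendar time, such as the component mix or the share of patients from each site, is then tied to length of follow-up. Table 1 says that program innovations arose asynchronously and were implemented variably, which makes such a change plausible without showing it.

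Counts of new diagnoses and health care use are the clearest case, because they grow with time observed. Symptom scores are affected only if they drift.

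This matters because the network is meant to show which treatments are more likely to give good long-term outcomes. The sections on the preimplementation stage and Conclusions carry those findings into implementing some components and deimplementing others. The planned bootstrap would not expose the problem: an edge produced by elapsed time is as stable under resampling as a real one.

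**Working it through.** **Sample.** The section on characterizing participants gives "Tampa site (n=approximately 350) and Richmond site (n=approximately 150". 350 + 150 = 500, which matches the survey figure. The article gives no power calculation and describes Aim 2 as exploratory.

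**Span of follow-up** (survey date minus discharge date, year 1 taken as October 2021 to September 2022).
- Discharged January 2015: 2021.75 − 2015.0 = 6.75 years, to 2022.75 − 2015.0 = 7.75 years.
- Discharged December 2015: 2021.75 − 2016.0 = 5.75 years, to 2022.75 − 2016.0 = 6.75 years.
- Counting year 1 from December 2021 raises the maximum to 7.9 years.
- New graduates, taking the anchor as program discharge: 0.5 to 0.75 years.
- Ratio: 5.75/0.75 = 7.7, to 7.75/0.5 = 15.5.

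If graduates were spread evenly over 2015-2022 (an assumption), median follow-up is about 3.3 years and the 10th to 90th percentiles are about 0.6 to 6.4 years.

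**Literal reading of the new-graduate timing.** A 3-year project begun in October 2021 completes about October 2024. Adding 6 to 9 months gives about April to July 2025. The Aim 2 output is due at the end of year 2, about September 2023, and data collection is expected to run through May 2025. Anchored on program discharge, a December 2022 graduate is surveyed in June to September 2023, which fits the year-2 date.

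**Possible size of the distortion.** None of the inputs here are in the documents. Assume 500 graduates spread evenly over 2015-2022, a component with no true effect, uptake changing linearly over the 8 years, and a score that drifts linearly with time since discharge.

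Hand check: users and non-users differ in mean discharge date by (yearly change in uptake) × (variance of discharge year) / (variance of use). The variance of discharge year is 8²/12 = 5.33. With average uptake 0.5, the variance of use is 0.25.
- Uptake 30% to 70%: 0.05 × 5.33/0.25 = 1.07 years.
- Uptake 10% to 90%: 0.10 × 5.33/0.25 = 2.13 years.

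Multiplying by the drift gives the spurious effect. A simulation (2000 runs per row, normal outcome with SD 1, component kept or dropped by the Bayesian information criterion) gives slightly smaller values, because new graduates are all surveyed at 6 to 9 months.

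| Drift, SD per year | Uptake | Hand check, SD | Simulated, SD | False edge, time omitted | False edge, time included |
|---|---|---|---|---|---|
| 0.05 | 30% to 70% | 0.053 | 0.05 | 2.1% | 1.1% |
| 0.05 | 10% to 90% | 0.107 | 0.10 | 8.2% | 1.6% |
| 0.10 | 30% to 70% | 0.107 | 0.10 | 8.3% | 1.4% |
| 0.10 | 10% to 90% | 0.213 | 0.20 | 36.5% | 1.2% |

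With no drift or constant uptake, the spurious effect is zero to within simulation error and false edges occur in 0.7% to 2.1% of runs. The mildest row is therefore close to harmless; only the steepest combination is serious.

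**The case against.** The article never says that survey times are pooled. Table 3 lists proposed measures by occasion and is not a model specification. The three levels are introduced to rule out impossible edge directions. An article may leave covariates, bands and windows to a fuller plan, and the long-term outcome survey is detailed in an appendix that is not shown. This stands in part: pooling is an inference. But the article goes beyond silence. It states the network levels and the conditioning set, and elapsed time is in neither.

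The analysis is also exploratory, and Potential Limitations admits that there is no comparison group. That lowers the stakes but does not remove them, since the findings are meant to guide deimplementation.

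Three stronger readings are tempting and are not supported.
- A reader might infer that early and late outcomes cannot be separated, against the Table 1 goal "Aim 2: determine early and late outcomes from IETP". Discharge versus survey is a natural reading of that goal, and Table 3 separates those.
- A reader might infer a very large bias. At an assumed 10% of patients per year with a new diagnosis, 1 − exp(−0.1 × 0.75) = 7.2% by 9 months and 1 − exp(−0.1 × 7) = 50.3% by 7 years, a gap of about 43 points. That needs an assumed rate, the two extremes of follow-up and a component used in one era only. It concerns cumulative diagnoses, not the Table 3 scores.
- A reader might take the Table 1 remark on asynchronous innovation as proof that component uptake changed by year. It describes variation in implementation and dates no component.

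**Conclusion.** The concern holds as a gap in the network as described. Follow-up differs between participants by a factor of roughly 8 to 15, and nothing in the stated levels or reported probabilities allows for it. Bias in component effects is conditional: component use or site mix must have changed over 2015-2022, and outcomes must drift or accumulate with time. The documents show neither change in uptake nor drift, so the size is unknown; 0.05 to 0.20 SD is an illustration, with zero as the lower bound. Exposure is clearest for new diagnoses and health care use, which have no stated window.

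The new-graduate timing is a wording slip, most likely for completion of the program. It should not add weight to the main point. Overall this is a cheap improvement to an exploratory analysis, of moderate severity and held with moderate confidence.

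**What to change.** 1. Compute time since discharge from discharge and survey dates. Allow it in the network as a root node that may be a parent of any outcome node.
2. Report survey outcomes, and the conditional probabilities for components, by band of time since discharge (for example under 1, 1 to 3, and over 3 years).
3. Count health-system outcomes in a common fixed window after discharge, or as rates per person-time. The window must be complete for the latest discharges when data are drawn: 12 months from December 2022 ends in December 2023, after the year-2 output date of about September 2023.
4. State that a component used in one era only cannot be separated from length of follow-up. Neither a time node nor bands can repair that.
5. Reword the new-graduate timing so that the 6 to 9 months run from completion of, or discharge from, the program.

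No new data collection should be needed, since the linked records should already hold the dates. The cost is precision: three time bands can triple an outcome's conditional table, and 500/3 is about 167 participants per band if they were even. Intervals will be somewhat wider, and events outside a fixed window would be described separately.
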